### **3.6.2 Randomization**

The randomization allocation to HPR, PTR, CON is performed using block randomization with a randomized block size of 6 and 12 in random order. The randomization list will be generated in REDCap by the trial statistician and is not accessible to investigators involved in the conduct of the study until the database has been unlocked.

After written informed consent and completion of study assessments, patients are randomized to either HPR, PTR or CON. The target number of patients randomized to each group is 70, 70 and 45 respectively. After identification of an eligible patient, the patient is assigned a randomization number as identifier throughout the study. The participants are informed about which group they are randomized to by email and phone call. The patients in the three groups begin their assigned intervention within seven to ten days after randomization.

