### **5. Recruitment of subjects, informed consent**

#### **5.1 Recruitment**

We will recruit through seven departments of respiratory medicine (Amager, Hvidovre, Bispebjerg, Herlev, Gentofte, Frederikssund and Hillerød University Hospitals) in the Capital Region of Copenhagen, through general practitioners and community healthcare centers to get a broad representative sample from the target population. Patients are continuously assessed against the study inclusion and exclusion criteria by the clinical staff (nurses or physicians).

The first invitation to this project takes place when patients are unable to access the conventional hospital- and community-based PR programs when offered during routine consultations and when inclusion and none of the exclusion criteria is confirmed by the clinical staff (nurses or physicians). The clinical staff receives patient consent to contact investigator. Subsequent the investigator will contact the patient 3-7 days after receiving the consent to contact from the clinical staff. Recruitment letter and participant information are post mailed to patient who consent to be contacted by the investigator. Recruitment letter and information material are also possible for the clinical staff to provide on beforehand if requested by the patient.

If a patient is suitable, the person will be invited to participate in the project. Participation in the trial is voluntary. Informed consent is obtained from the participants by executive order no. 1149, 30th September 2013 with information and consent for participation in health science research projects as well as on notification of health science research projects.

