### **6.2 data storage**

An electronic case report form (Research Electronic Data Capture, REDCap) is provided and all data related to the study are recorded providing the basis for a central database. In this central database, data are stored in coded form according to the rules of the Danish Data Protection Agency (Datatilsynet). The electronic case report form (e-CRF) is to be completed by blinded assessors at the time of the participant's assessments time-points, so that it always reflects the latest observations for the patient. Data will be stored for 10 years, after which they will be transferred to The Danish National Archives ("Rigsarkivet"). Source data are registered directly in the e-CRF.

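### Section 3.6.2 prints the block sizes in an open trial and releases the allocation list when the database is unlocked rather than locked

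*Protocol*

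**What the plan says.** Protocol section 3.6.2 describes "block randomization with a randomized block size of 6 and 12 in random order". The trial statistician generates the list in REDCap, and it "is not accessible to investigators involved in the conduct of the study until the database has been unlocked". On numbers: "The target number of patients randomized to each group is 70, 70 and 45 respectively". On timing: "After written informed consent and completion of study assessments, patients are randomized to either HPR, PTR or CON". No stratification factor, allocation ratio or block composition is given.

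Assignments do not stay hidden once made: "The participants are informed about which group they are randomized to by email and phone call". Section 5.1 gives the recruitment route. It begins "We will recruit through seven departments of respiratory medicine", and adds general practitioners and community health centres. Clinical staff screen patients and ask permission for contact, and then "Subsequent the investigator will contact the patient 3-7 days after receiving the consent to contact from the clinical staff". Under section 6.2 (data storage) the electronic case report form "is to be completed by blinded assessors at the time of the participant's assessments time-points".

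**The concern.** In a trial with open arms, concealment of the next assignment depends on recruiting staff being unable to work it out. Two statements in section 3.6.2 weaken that.

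First, the block sizes appear in the protocol. There are only two, and one is twice the other, so every block ends at a multiple of six on a single unstratified list. A person who knows this and has followed the sequence can sometimes tell that an arm is used up in the current block.

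Second, the release condition runs the wrong way. A database is unlocked while data are being entered and is locked afterwards. The sentence is meant to keep investigators away from the list, but as written it sets no usable end point, or allows access during recruitment.

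What is at stake is selection at entry. Randomisation after consent and baseline assessment limits this, but the timing of contact and the judgement that a patient is unable to access conventional rehabilitation both come before randomisation. The primary outcome (CAT) is completed by patients who know their arm.

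**Working it through.** **Inputs.** Block sizes 6 and 12, total 185, target 70/70/45 and seven hospital departments come from sections 3.6.2 and 5.1. The protocol gives no figure for predictability, so there is none to reproduce. Three things are assumed: the two sizes are equally likely, blocks are split equally between arms, and patients reach sites at random.

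**Step 1: is the equal split the planned one?** The target needs 70/185 × 6 = 2.27 and 45/185 × 6 = 1.46 patients per block of 6, and 4.54 and 2.92 per block of 12. None is a whole number. Equal blocks would give 185/3 = 61.7 per arm, which is not the target. The equal split is therefore a working assumption.

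**Step 2: the guessing rule.** The observer weighs each possible state of the current block by its probability given the history:

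P(next = arm a) = Σ (weight of state) × (places left for a) / (places left in the block).

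Suppose the list opens A, A, B, B, C.
- Under a block of 6 this has probability (2·1·2·1·2)/(6·5·4·3·2) = 8/720 = 0.0111, and only C is left.
- Under a block of 12 it has probability (4·3·4·3·4)/(12·11·10·9·8) = 576/95,040 = 0.0061, and C has 3 of the 7 remaining places.
- The weight on the block of 6 is 0.0111/(0.0111 + 0.0061) = 0.65, so P(C) = 0.65 + 0.35 × 3/7 = 0.80.

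Certainty needs the sizes. If the first three assignments go to one arm, a 2:2:2 block is impossible, the block must be 12, and its last place is known in advance. An observer who does not know the sizes cannot conclude this.

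**Step 3: simulation of 185-patient lists, equal split.**

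| List and observer | Correct guess | Certain | At least one arm ruled out |
|---|---|---|---|
| Chance | 33.3% | – | – |
| 6 and 12, sizes known, full history | 52.5% | 5.6% | 15.4% |
| 6 and 12, sizes unknown, picks the arm with fewest patients, full history | 52.5% | not possible | not possible |
| 12, 15, 18, 21 and 24, sizes known, full history | 48% | 0.6% | 2.0% |

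The third column is part of the fourth. In patients, 5.6% of 185 is about 10 and 15.4% is about 28. With the larger blocks these become about 1 and 4. A separate run for this write-up gave 52.8%, 5.5% and 15.2% for blocks of 6 and 12, and 48.4%, 0.5% and 1.8% for the larger set. The differences are simulation noise.

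**Step 4: how much of the sequence is seen.** With blocks of 6 and 12 and known sizes, correct guesses fall to about 39% for someone who sees half of all patients, 38% for one third, and 35% to 37% for one seventh.

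**Step 5: unequal blocks.** For several unequal whole-number compositions and full history, correct guesses were 51% to 55% against 36% to 39% by chance, with 2% to 6% certain. This requires knowing the exact composition, which the protocol does not print. Without it the rate was 41% to 43%.

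**The case against.** The strongest reply is that disclosure does little. On the equal-split model, choosing the least-filled arm with no knowledge of the sizes does as well on average as the best rule with that knowledge. This stands. The 53% must not be presented as a result of printing the sizes; disclosure adds only the certain and ruled-out cases.

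A reader might infer that every recruiter can predict the next arm. The protocol does not support that. Nothing in it says that referring clinicians, general practitioners or health centres see the running sequence, and someone who sees one site's patients is near chance. The inference is more reasonable for the central team: section 3.5 has one project manager running daily work with a project group that helps recruit, section 3.3 places the practical work in three research units, and section 5.1 has the investigator make contact. The protocol neither says who sees cumulative assignments nor separates them from recruitment.

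A reader might also infer a definite bias in CAT or an inflated type I error. Any such figure needs an assumed shift in case mix that the protocol does not give, and section 3.6.1 plans a model adjusted for baseline and other covariates. None is claimed here.

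Finally, a reader might take the release wording to mean that the list is actually open during recruitment. The purpose of the sentence is to deny access, so a slip is the likelier explanation, and the wording does not by itself make assignments guessable. The safeguards in the plan are real: random block order, a list closed to investigators, randomisation after consent and assessment, and blinded assessors. They do not make it necessary to print the sizes or leave the release rule as written.

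**Conclusion.** The point holds as a modest defect of concealment that is cheap to correct. The protocol discloses the block sizes of a single unstratified list in an open trial, and it states the release condition the wrong way round.

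For a central recruiter who knows the sizes and follows the whole sequence, about 6% of assignments would be certain and about 15% would have at least one arm ruled out. Those figures rest on an equal split within blocks, a 50:50 mix of sizes and full sight of the history. The split cannot be exactly what is planned, because equal blocks miss 70/70/45. Under the unequal compositions tried, certainty ranged from 2% to 6%. The overall guess rate is a property of small blocks with visible history.

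**What to change.** 1. Remove the block sizes from section 3.6.2. State that sizes vary at random and are held in a restricted document not available to staff who recruit, consent, assess or treat. Generate the unused part of the REDCap list with several larger, undisclosed sizes whose composition delivers the target. For example, a 3:3:2 ratio gives 185 × 3/8 = 69.4, 69.4 and 185 × 2/8 = 46.3. The expected gain is mainly in certain and ruled-out assignments; the guess rate improves only modestly.
2. Change the release condition so that investigators have no access until the database has been locked, and name the follow-up visit to which that lock refers.

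The cost is a short amendment, one restricted document and a regenerated list. Balance between arms is slightly looser if recruitment stops inside a larger block. No extra patients or procedures are needed. If all assignments have already been issued, regeneration no longer applies; the wording should still be corrected, and the report should say who could see the list and the cumulative assignments.

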## **3.7 Interventions (also read figures in appendices 1)**

### **3.7.1 Pulmonary Tele-Rehabilitation (PTR)**

The PTR intervention is supervised by skilled physiotherapists and respiratory nurses with at least 2-years of substantial experience with PR and delivered via a virtual platform at Bispebjerg and Hvidovre Hospital to a group of 4–6 patients who exercise at home and communicate via tablet with Center for IT and Medico (CIMT) approved communication software. Each session is 60 min; 35 min of exercise and 25 min of patient education, two times per week for the duration of 10 weeks. The specific exercises used are evidence-based as they have been used in several intervention studies on patients with severe or very severe COPD and involves larger muscle groups with 50/50% exercises for upper and lower extremities, respectively. Volume, intensity and content specified for the exercise protocol is in accordance with both national and international exercise recommendations. The exercise sessions include relative progression every fourth week, as the patients are expected to improve their mental and physical capacity during the intervention. Additionally, to the supervised program, patients are instructed to do daily physical activity of at least 30 minutes by modalities accessible to the patient, e.g. in- or outdoor walking activities in bouts of minimum 10 minutes.

Every second session of the patient education consists of 25 minutes of Mindfulness-based Cognitive Therapy (MCBT) exercises and education developed for COPD patients with the potential mediating effects of mindfulness, self-compassion and breathlessness catastrophizing. The other education sessions consist of dialogue reflections around empowerment of the subjects: action-plan for symptom deterioration, medication-technic and correct use, better living with COPD, nutrition and importance of smoking cessation.

The physical exercises are available on the tablet as instructed exercise-film for self-initiated exercising. The mindfulness exercises are available from sound-files on the tablet for self-initiated mindfulness-guidance. Educational material is delivered in hard copies together with tablet and exercise equipment but also available as audio-book chapters on the tablet in layman language. The book is called Better Living with Chronic Obstructive Pulmonary Disease – a patient guide. Exercise equipment is a package of a step-box and pairs of dumbbells weight from 1 to 5 kilo (heavier dumbbells available on request).

### **3.7.2 Home-based Pulmonary Rehabilitation (HPR)**

The HPR intervention is an individual self-initiated home-based PR program with motivational and professional counseling, supported by health technology e.g. telephone call and facetime with choice of preference. The first session is a home visit by an experienced respiratory physiotherapist/nurse. During the visit the physiotherapist/nurse works with the patient to establish exercise goals, write a formal exercise prescription of four to six exercises, provide a mindfulness program and education in use of a home diary and assess inhaler technique. The physiotherapist also supervises the first exercise and mindfulness session. The patient is informed that performing the self-initiated exercise and mindfulness program is likely to improve their symptoms, fitness and physical functioning.

The overall goal is for the patient to achieve at least 30 minutes of self-initiated muscle-endurance based exercise three days a week. The prescribed physical exercises are available on the tablet as an instructed exercise-film. Secondly the patient is instructed to complete a mindfulness program of choice for 15 minutes at least once a week. Seven mindfulness exercises are available from sound-files on the tablet for self-initiated mindfulness-sessions.

Additionally, daily physical activity of at least 30 minutes by modalities accessible to the patient, e.g. in- or outdoor walking activities in bouts of minimum 10 minutes. During the initial visit the physiotherapist/nurse accompanies the participant on their initial walk (weather permitting for those who had chosen to walk outside the home). This allows planning of an appropriate route around the local neighborhood consistent with the patient's abilities (e.g. ability to walk stairs/hills).

In a home diary the patient is instructed to record when, where and how often she/he plans to perform exercise and mindfulness; what might get in the way of the plans this week; and what can be done to overcome any perceived barriers. The diary includes a telephone number so the patient can contact the physiotherapist/nurse between sessions if required to answer questions related to the program. During the initial home visit the physiotherapist/nurse also assesses safety of the home environment in relation to the exercise program.

The home visit is followed by once weekly structured web/phone call from the physiotherapist/nurse for 10-weeks using a motivational interviewing approach. During the telephone calls, the patient discusses the exercise, mindfulness program and exercise goals, and have the option to discuss other health issues in relation to COPD. A typical telephone call will begin with a brief talk of what has happened during the exercise program over the past week. Consistent with the principles of motivational interviewing, the physiotherapist/nurse might then ask the patient why she/he might want to increase the exercise program (desire); how she/he might do this if she/he decides to (ability); what would be the most important benefits in doing more exercise (reasons); and how important it is for the patient to do more exercise at this time (need). The physiotherapist will then encourage the participant to move towards commitment and action, with specific goal set for the following week. During each web/phone call the participants document their goals in their diaries in the same manner as from the initial home visit session. The discussion will then move on to other issues in relation to COPD. The patient is provided with a menu of topics relevant to COPD and self-care and encouraged to select a topic of relevance for discussion, providing opportunity for self-management. Education materials are delivered in hard copies together with the tablet and exercise equipment but also available as audio-book chapter on tablet in layman language. The book is called Better Living with Chronic Obstructive Pulmonary Disease – a patient guide. Exercise equipment is a package of a step-box and pairs of dumbbells weight from 1 to 5 kilo (heavier dumbbells available on request).

### **3.7.3 Control**

Patients randomized to the control group will receive usual care; medication, scheduled follow-up visit and possible phone contact with GP or the outpatient respiratory department. Except for assessment visits 10-, 35-, and 75-weeks from baseline no intervention is offered.

If a patient changes his/her mind and wishes to participate in a conventional hospital- or community-based PR program, it will be granted as this is a highly recommended treatment (e.g. rehabilitation after hospital admitted exacerbation).

### **3.7.4 Maintenance**

During the 15-month maintenance program, patients are asked to continue at home with a similar program to that completed. The weekly goal is for the patient to achieve at least 30 minutes of self-initiated muscle-endurance based exercises twice weekly, complete a mindfulness program of choice for 15 minutes at least once a week and, in addition they are once weekly offered healthcare professional (physiotherapist/nurse) supervised exercise (groups of 4-6 persons), mindfulness and dialogue/consultation for 60 minutes throughout the 15-month maintenance period.

The prescribed physical exercises are available on the tablet as an instructed exercise-film. Seven mindfulness exercises are available from sound-files on the tablet for self-initiated mindfulness-guidance.

The overall goal for the maintenance program is that the patient achieves sustainable exercise habits and maintain or even improve gains from the intervention.

### **3.7.5 Use of hardware and software technology for intervention delivery**

The Capital Region of Copenhagen will provide android tablets with the pre-developed tools/e-tools, online exercise programs, internet installed and provide delivery and full service including the exercise equipment.

The system is approved by Center for IT and Medico-Technology (CIMT) and the data protection agency. The screen is a Samsung tablet touch screen, with a single interface that can be operated by all patients. The screen for healthcare professionals consists of a professional video conferencing system that makes it possible to see multiple patients during a training session and train the group synchronously in real time. The product supports the possibility of group training via video conference and is already used for other telemedical consultations.

The research staff has in-dept knowledge and experience with the technology. From our previous telerehabilitation study, we documented that major technical issues leading to cancellation and rescheduling of group sessions affected 2 of 360 group sessions. Minor temporary technical issues (that is sound artefacts, screen freezes) not leading to cancellation or delay were present in 14% of the total group session (49 of 360). Individual patient cancellation caused by technical problems was 12 of 1902 individual connections.

## **4. Risk, harms, and side effects**

As mentioned above, pulmonary rehabilitation is considered cornerstone treatment to patient with severe COPD. Even though COPD leads to profound pathophysiological changes, exercise training has minimal risks. The risks associated with participation in the REPORT study are considered minimal, as both interventions are developed based on current guideline recommendations on physical exertion, exercise and activity for patients with COPD.

We are not aware of any serious circumstances (death, hospitalization, serious injury related to the functional tests) from clinical studies or clinical practice in related patient groups that have undergone similar functional test which has led to termination of the trial as a whole or any specific functional test. Subjects should anticipate the possibility of muscle soreness that typically lasts one to two days after assessments. Neither the examination nor the physical tests are more intrusive to regular out-patient examination after respiratory exacerbations. A few safety precautions described below are applied for the participants in the study.

#### **4.1 Assessment of safety**

Information about adverse events and serious adverse events related to the interventions, whether reported by the participant, discovered by the researchers by reviewing medical records, detected through examinations during assessment-visits, through tests or other means, that occur from the time the informed consent form is signed by the patient and until assessment-visit 3 will be recorded and reported on an adverse event page in the e-CRF. Evaluation of adverse events and serious adverse events, including severity, causality, outcome and seriousness assessments, will be performed by a senior physician ([name], [name] and [name]) and reviewed by the international advisory board.

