| Data registrations and
expense indicators | Adherence to intervention/self-maintenance   |                                                                          | X                                 | X                      | X                      |
|                                              | Adverse events recorded                      |                                                                          | X                                 | X                      | X                      |
|                                              | Number of hospital admission                 | past 12-mo                                                               | X                                 | X                      | X                      |
|                                              | Length of stay – hospital admission          | past 12-mo                                                               | X                                 | X                      | X                      |
|                                              | Consultant visits                            | past 12-mo                                                               | X                                 | X                      | X                      |
|                                              | Mortality                                    |                                                                          | X                                 | X                      | X                      |
|                                              | Comorbidities                                | X                                                                        | X                                 | X                      | X                      |
| Descriptive variable                  |                                              |                                                                          |                                   |                        |                        |
| Lung function test                           | FEV1/FVC ratio in %                          | X                                                                        |                                   |                        | X                      |

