| Control group       | 
 
• Patients randomized in the control group will receive usual care; medication, contact and scheduled controls for the first 10 weeks. After 10 weeks, controls will be offered to participate in the maintenance exercise program for 15-month (65-weeks) free of charge or to continue as control without maintenance. The 10-, 35- and 75-weeks follow-up from baseline is the same as the intervention groups. If a patient changes their mind and wish to participate in a conventional hospital- og community-based PR program, it will be granted since this is a high recommended treatment (e.g. rehabilitation after hospital admitted exacerbation).
 
                                                              |
| Maintenance program | 
 
• During the 15-month maintenance program, patients are asked to continue at home with a similar program to that completed in the intervention twice weekly with tablet and exercise equipment available and they are additionally offered group supervised exercise, mindfulness and dialogue/consultation (physiotherapist/nurse) once weekly for 60 minutes throughout the 15-month maintenance period. The overall goal for the patient is to achieve sustainable exercise habits and maintain or improve gains from the intervention.
 
                                                                                                                                                                                   |

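### Section 4.1 makes relatedness to the intervention a condition for recording an adverse event, which leaves usual care with almost nothing to record up to week 10 and biases comparison of events other than admissions, deaths and fractures

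*Protocol*

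**What the plan says.** Section 4.1 is the only place that defines what goes on the adverse event page. Its scope is "Information about adverse events and serious adverse events related to the interventions", and its window covers events "that occur from the time the informed consent form is signed by the patient and until assessment-visit 3". Sources are the participant, review of medical records, and examinations and tests at assessment visits. The same section then assigns the judgement of these events, "including severity, causality, outcome and seriousness assessments, will be performed by a senior physician", with review by the international advisory board.

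Table 1 (under Outcomes) has a row "Adverse events recorded", marked at weeks 10, 35 and 75, with no limit by relatedness or by arm. Section 6.2 (data storage) has blinded assessors complete the e-CRF at the assessment time-points.

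On the control arm, section 3.7.3 states: "Except for assessment visits 10-, 35-, and 75-weeks from baseline no intervention is offered". The control row of the intervention table in Appendices 1 states: "After 10 weeks, controls will be offered to participate in the maintenance exercise program".

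**The concern.** The condition is applied at the point of recording, before anyone has been asked to judge cause. An event taken to be unrelated when it first comes to light never reaches the physician whose task is to judge relatedness. In a three-arm trial with a no-intervention control the effect is also lopsided: an exacerbation or a fall in HPR or PTR can be entered if somebody thinks the programme contributed, while the same event in usual care has no intervention to be related to.

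What is at stake is the non-serious and non-admitted part of the harms data. HPR is largely self-initiated exercise at home, supervised in person at the first session (section 3.7.2), and patients may enter with a walking aid (section 3.4.1). Minor falls, strains and exacerbations managed outside hospital are the events most likely to be missed. This is a matter of data collection, so a separate statistical analysis plan cannot repair it.

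**Working it through.** There is no stated figure to reproduce. The check sets the passages side by side.

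**1. Scope against causality (both section 4.1).** The page admits related events; the physician then assesses causality. If the first rule is followed, the second can only confirm or overturn positives. False negatives at entry are never seen.

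**2. Scope against window.** Recording opens at consent. Under section 3.6.2, randomisation comes after consent and the baseline assessments, and interventions begin seven to ten days after randomisation. No event in that interval can be related to an intervention, so the opening of the window has no content under the literal scope. Section 4 expects muscle soreness after the assessments, which all arms undergo; such events come from the tests and would also fall outside the scope.

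**3. Scope against Table 1.** The adverse event row applies to all patients at three visits without qualification. Both texts cannot be followed.

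**4. Scope against blinding.** An assessor blinded to arm cannot decide whether an event is related to an intervention. At assessment visits the condition is either unworkable or applied by someone who knows the allocation. The protocol does not say which.

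**5. Effect on the comparison up to week 10.** Let p be the all-cause event risk in every arm, so the true excess is zero, and let f be the share of intervention-arm events that staff regard as related. The page then shows about f × p in HPR or PTR and about 0 in usual care, an apparent excess of f × p. Conversely, a real reduction in exacerbations under rehabilitation could not appear, because the control events it would be measured against are not entered.

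**6. What is collected regardless of cause.**

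| Item | Where | All arms? |
|---|---|---|
| Admissions, length of stay, mortality | 2.1.3 aim 2, 3.5.2, Table 1 | Yes |
| Fractures | Table 1 | Yes |
| Between-group test of hospitalisation and death | 3.6.1 | Yes |
| Other adverse events | 4.1 | Only if related, on a literal reading |

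**7. Opportunity to report, to week 10.** Programme contacts are PTR 2 sessions × 10 weeks = 20, HPR 1 home visit + 10 weekly calls = 11, and control 0. Adding the week-10 visit that every arm has gives 21, 12 and 1. These counts leave out medical-record review and usual-care contacts, so they overstate the gap for documented events. They bear mainly on minor events that a patient merely mentions.

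**8. How much the fix can deliver.** The protocol gives no adverse event rates, so these are assumptions. With 70 against 45 patients and a two-sided 5% level, power is approximately Φ[(d − 1.96·s0)/s1], where d is the difference in proportions, s0 its standard error with pooled proportions and s1 with separate ones. For 20% against 40%, s0 = 0.0893 and s1 = 0.0836, so (0.200 − 0.175)/0.0836 = 0.30 and power is about 0.62. For 20% against 45% it is about 0.80. For a 20-point excess over control rates of 10% to 40% it runs from about 0.74 down to 0.55. Full recording therefore supports an unbiased estimate, but a formal test only of large differences.

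**The case against.** The strongest reply is that the phrase is loose drafting and broad recording was intended. Table 1 is unrestricted, the window opens at consent, causality is a separate step, and grammatically the qualifier could attach to serious events alone. That is a fair reading. It does not remove the point, because section 4.1 is the text that staff will follow when deciding what to enter, and two sites could follow it differently.

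A reader might infer that harms cannot be compared between arms at all. The documents do not support that: the gravest outcomes and fractures are captured irrespective of cause, and hospitalisation and death are tested between groups.

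A reader might also infer an empty control column through to visit 3. That fails too. Appendices 1 lets controls join a 65-week maintenance programme after week 10, so related events become possible in that arm, although section 3.7.3 reads otherwise.

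Nor does the protocol say that unblinded treating staff apply the filter; it names nobody. Unequal contact is inherent in comparing supervised programmes with usual care and is not in itself a fault, and record review narrows it.

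Finally, no objective concerns adverse event rates, section 3.6.1 names no between-arm test of them, and section 4 rates the risk as minimal. So no planned analysis fails. What is affected is the harms table that any report of the trial will carry.

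**Conclusion.** The point holds in a limited form. Section 4.1 ties recording to a causality judgement that it assigns to a later step, and this conflicts with its own window, with Table 1 and with blinded completion of the e-CRF. On a literal reading, usual care has almost no recordable event up to week 10. Comparison of events other than admissions, deaths and fractures is then biased by an amount that cannot be estimated from the documents, since they give neither event rates nor the share likely to be called related.

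This rests on two assumptions: that the qualifier covers all adverse events and not serious ones alone, and that staff follow section 4.1 where it differs from Table 1. After week 10 the size of the problem depends on whether controls are offered maintenance, on which the protocol contradicts itself. It is a cheap improvement worth making, and it does not threaten the primary analysis.

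**What to change.** In section 4.1, remove relatedness as a condition for recording. State that all adverse and serious adverse events are recorded in all three arms from consent to visit 3, and that the senior physician assigns causality afterwards.

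Ask about events with the same standard questions in every arm at weeks 10, 35 and 75, in line with Table 1. Base between-arm comparison on these visit-elicited events together with the admission, death and fracture data. List events that surface at PTR sessions or HPR calls separately.

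Reconcile section 3.7.3 with the control row in Appendices 1 on whether controls are offered maintenance after week 10, because that determines which control events could be related to an intervention.

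The cost is a reworded sentence or two, a common set of questions, and an e-CRF field marking how each event came to light. Event entry will rise, and over 75 weeks in 185 patients with moderate to very severe COPD the increase may not be trivial. The visits, the adverse event page and the physician review already exist.
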